# A randomised phase II trial of temozolomide with or without cannabinoids in patients with recurrent glioblastoma (ARISTOCRAT): protocol for a multi-centre, double-blind, placebo-controlled trial

**DOI:** 10.1186/s12885-023-11792-4

**Published:** 2024-01-15

**Keywords:** Randomised phase II trial, Glioblastoma, Cannabinoids, Sativex, Nabiximols, Brain cancer, Tumour, Temozolomide, Progression free survival, Overall survival, Adverse events

## Abstract

**Background:**

Glioblastoma (GBM) is the most common adult malignant brain tumour, with an incidence of 5 per 100,000 per year in England. Patients with tumours showing O^6^-methylguanine-DNA methyltransferase (MGMT) promoter methylation represent around 40% of newly diagnosed GBM. Relapse/tumour recurrence is inevitable. There is no agreed standard treatment for patients with GBM, therefore, it is aimed at delaying further tumour progression and maintaining health-related quality of life (HRQoL). Limited clinical trial data exist using cannabinoids in combination with temozolomide (TMZ) in this setting, but early phase data demonstrate prolonged overall survival compared to TMZ alone, with few additional side effects. Jazz Pharmaceuticals (previously GW Pharma Ltd.) have developed nabiximols (trade name Sativex®), an oromucosal spray containing a blend of cannabis plant extracts, that we aim to assess for preliminary efficacy in patients with recurrent GBM.

**Methods:**

ARISTOCRAT is a phase II, multi-centre, double-blind, placebo-controlled, randomised trial to assess cannabinoids in patients with recurrent MGMT methylated GBM who are suitable for treatment with TMZ. Patients who have relapsed ≥ 3 months after completion of initial first-line treatment will be randomised 2:1 to receive either nabiximols or placebo in combination with TMZ. The primary outcome is overall survival time defined as the time in whole days from the date of randomisation to the date of death from any cause. Secondary outcomes include overall survival at 12 months, progression-free survival time, HRQoL (using patient reported outcomes from QLQ-C30, QLQ-BN20 and EQ-5D-5L questionnaires), and adverse events.

**Discussion:**

Patients with recurrent MGMT promoter methylated GBM represent a relatively good prognosis sub-group of patients with GBM. However, their median survival remains poor and, therefore, more effective treatments are needed. The phase II design of this trial was chosen, rather than phase III, due to the lack of data currently available on cannabinoid efficacy in this setting. A randomised, double-blind, placebo-controlled trial will ensure an unbiased robust evaluation of the treatment and will allow potential expansion of recruitment into a phase III trial should the emerging phase II results warrant this development.

**Trial registration:**

ISRCTN: 11460478. ClinicalTrials.Gov: NCT05629702.

**Supplementary Information:**

The online version contains supplementary material available at 10.1186/s12885-023-11792-4.

## Background

Glioblastoma (GBM) is the most common adult malignant brain tumour, with an incidence of 5 per 100,000 per year in England [1]. Prognosis is poor, with the majority of patients surviving less than one year and the average years of life lost to a brain tumour being 20.1, compared to breast cancer at 13.5 [2]. Treatment is palliative in nature from diagnosis, aimed at delaying disease progression and managing symptoms/preserving health-related quality of life (HRQoL). Optimal first-line treatment includes debulking surgery (if feasible), followed by chemo-radiotherapy and adjuvant chemotherapy using temozolomide (TMZ) (Stupp regimen) [3]. Despite this intensive treatment, median progression free survival time (PFS) is 6.9 months and median overall survival time (OS) 14.6 months [3]. At the time of inevitable disease recurrence, the aim remains broadly similar to first line treatment; delaying further progression and maintaining HRQoL. There is no agreed standard treatment, therefore, treatment decisions are made on a case-by-case basis [4].

Response to TMZ is an important determinant of outcome. Patients with O^6^-methylguanine-DNA-methyltransferase (MGMT) promoter methylated tumours have better outcomes from treatment with TMZ, compared to those with promoter unmethylated tumours [5, 6]. Patients with tumours showing MGMT promoter methylation represent around 40% of newly diagnosed GBM [7, 8]. Common practice includes a further course of TMZ in those patients with MGMT methylated tumours who relapse more than six months after completing adjuvant TMZ.

Phytocannabinoids occur naturally in cannabis plants and have been used medicinally for centuries for a variety of purposes [9]. Δ9-tetrahydrocannabinol (THC) is the major psychoactive constituent in cannabis, and cannabidiol (CBD) the major non-psychoactive constituent. Activation of the cannabinoid receptors, CB1 and CB2, exerts various downstream signalling effects, with diverse consequences on cellular biology and functions [10]. Glioblastomas express both CB1 and CB2 [11], with high-grade tumours expressing high levels of CB2. In vivo studies have found that the administration of CBD and THC reduced tumour growth in animal models of glioma [12]. These effects are thought to be mediated by induction of cell death (via apoptosis or cytotoxic autophagy), inhibition of cell proliferation, and anti-angiogenic effects [13]. Specific to GBM, combined administration of THC and TMZ exerts strong anti-tumoural effects in glioma xenografts, an effect maintained in tumours resistant to TMZ treatment [14]. In a trial investigating the effects of intracranial THC (100 mg/ml in ethanol) in patients with recurrent GBM, a reduction in tumour cell proliferation was reported in two of nine patients [15].

Jazz Pharmaceuticals (previously GW Pharma Ltd.) have developed nabiximols (trade name Sativex®), an oromucosal spray of a complex botanical mixture containing THC and CBD as the principal cannabinoids, with additional cannabinoid constituents and non-cannabinoid components, and was the first cannabis-based medicine to be licensed in the UK for multiple sclerosis spasticity. A two-part safety and exploratory efficacy randomised phase I double blind, placebo-controlled trial of nabiximols in combination with dose dense TMZ in 21 patients with relapsed GBM suggested that combination nabiximols/TMZ may be associated with prolonged OS compared to TMZ alone (observed hazard ratio < 0.5). In this trial, 12 patients received nabiximols and 9 placebo due to an imbalance in randomisation meaning that the interpretation of OS needed to be done with caution [16]. The most common adverse events (AEs) reported were vomiting, dizziness, nausea, fatigue, and headache, most commonly Common Terminology Criteria for Adverse Events (CTCAE) grade 2 and 3, and there was no difference in the incidence of treatment emergent AEs between the treatment groups [16]. There was no interaction documented between nabiximols and TMZ [16].

These data require confirmation in the setting of a larger randomised study in which known biomarkers of response to treatment, including MGMT status, are accounted for. Therefore, the ARISTOCRAT trial will assess whether the addition of cannabinoid (nabiximols) to standard TMZ treatment in patients with recurrent MGMT methylated GBM improves disease outcomes.

## Methods

### Trial design

ARISTOCRAT is a phase II, multi-centre, double-blind, placebo-controlled, randomised trial to compare nabiximols with placebo in patients with recurrent MGMT methylated GBM suitable for treatment with TMZ. The trial has a target sample size of 234 patients who will be randomised on a 2:1 basis to receive either nabiximols or placebo, respectively, in combination with standard TMZ treatment (Fig. 1). The trial includes an initial feasibility study of 40 patients to confirm safety, compliance, and achievability of planned target recruitment. There are no formal criteria for evaluating feasibility but once 40 patients have been recruited, the independent Data Monitoring Committee (DMC) will review AE data, details on protocol treatment received, monthly recruitment rates and projected recruitment to make recommendations on trial continuation.

**Fig. 1 Fig1:**
[figure not shown]
ARISTOCRAT trial schema Overview of ARISTOCRAT trial GBM: Glioblastoma; MGMT: O^6^-Methylguanine-DNA-methyltransferase

The phase II trial design will enable potential expansion of recruitment into a phase III trial, should the emerging phase II results warrant this. Should this occur, funding will be sought, and the protocol amended.

A list of the ARISTOCRAT trial sites can be requested from the ARISTOCRAT Trial Office ([contact]). The Standard Protocol Items: Recommendations for Intervention Trials (SPIRIT) checklist [17] is provided in Appendix 1. The World Health Organization (WHO) Trial Registration Data Set is provided in Appendix 2.

### Randomisation and blinding

Randomisation is on a 2:1 basis to receive either nabiximols or placebo and stratified by age (≤ 70 vs. > 70 years), performance status (Karnofsky PS 60–79 v 80–100), and sex (male vs. female) in a double-blinded manner.

Treatment allocation is performed by central randomisation at the Cancer Research UK Clinical Trials Unit (CRCTU), University of Birmingham following submission of the completed Randomisation Form on the electronic Remote Data Capture (eRDC) system. A standard minimisation procedure is being used to allocate patients into the two arms to ensure a balance between the stratification variables.

Each patient will be assigned a unique Spray Vial Allocation Number, which will correspond to the Spray Vial Allocation List provided to local pharmacy at the site initiation. This list is strictly for pharmacy staff and will not be disclosed to any of the other members of the clinical team at the site to maintain blinding. The local pharmacy will then blind the appropriate medication for that patient. Neither the investigator nor the patient will know which combination is being administered.

Emergency unblinding will only be available in the event of patient safety concerns, this can be performed via the ARISTOCRAT Trial Office or via the site pharmacy using the eRDC system or paper allocation list.

### Patient and public involvement

Patient and public involvement and engagement (PPIE) has been integral to this study from its inception. The study was discussed by patients at The Brain Tumour Charity’s Research Involvement Network, and feedback received was used in developing the trial design. Our patient and public advisor, [name], co-developed the ARISTOCRAT trial by reviewing and refining the protocol and the participant-facing documents. He has provided input into the patient-reported outcome measures and has guided messaging about the study for the community. As a member of the Trial Management Group (TMG), he continues to assess trial conduct and will contribute to the interpretation and dissemination of study findings. A second PPIE representative, [name], sits on the Trial Steering Committee (TSC).

A video interview was recorded between the Chief Investigator and a GBM patient as an educational tool for the trial and was posted online. In addition, a patient-facing website has been developed with our PPIE representatives and is hosted by the University of Birmingham (www.birmingham.ac.uk/aristocrat), along with lay-friendly materials posted to The Brain Tumour Charity’s website.

Our ongoing plans for dissemination include a webinar hosted by The Brain Tumour Charity to be held following the launch of the trial to update patients, the public, and supporters.

### Patient recruitment

This trial aims to recruit patients at UK participating centres following referral from their local multidisciplinary team at point of recurrence, including confirmation of radiological recurrence from a consultant neuro-radiologist. Recruitment will be over three years, with participants followed up for at least one year from the start of treatment or until death. Key eligibility criteria are listed in Table 1.

**Table 1 Tab1:** Key eligibility criteria for ARISTOCRAT

**Inclusion criteria**
Age ≥ 16
Karnofsky Performance Status ≥ 60
Histological diagnosis of MGMT promoter methylated, IDH wild type GBM with consistent local molecular pathology
First recurrence of GBM planned for systemic treatment are most in keeping with recurrence and not pseudo-progression and patient is planned for systemic treatment
Patients must have received initial first-line treatment with standard dose conventionally fractionated radiotherapy (i.e., 40 Gy in 15 fractions or 54-54-60 Gy in 28–33 fractions; other regimes may be considered in consultation with the ARISTOCRAT Trial Office) with concomitant and adjuvant TMZ
• A minimum of 3 cycles of adjuvant TMZ must have been received
• A minimum of SD (or PR/CR) at the end of first-line treatment
≥ 3 months since day 28 of the last cycle of TMZ
Adequate hematologic, renal, and hepatic function within 14 days prior to randomisation
**Exclusion criteria**
Pathology inconsistent with IDH wild type GBM
Prior invasive malignancy (except non-melanoma skin cancer), unless disease free for a minimum of one year
Prior treatment with stereotactic radiotherapy, brachytherapy, or convection enhanced delivery of any agent
Prior treatment, apart from debulking surgery, for first recurrence of GBM
Personal history of schizophrenia, other psychotic illness, severe personality disorder or other significant psychiatric diagnosis other than depression associated with their underlying glioma condition
Prior allergic reaction or significant toxicity (≥ Grade 3 CTCAE) related to TMZ treatment
Current or recent cannabis or cannabinoid-based medications within 30 days of randomisation and/or unwilling to abstain for the duration of the trial
Women who are pregnant, breastfeeding or a woman of childbearing potential who is unwilling to use effective contraceptive methods during trial treatment and for 6 months after completion of trial treatment
• Women of childbearing age must have a negative pregnancy test within 7 days prior to randomisation
Men who are sexually active and unwilling/unable to use medically acceptable forms of contraception during trial treatment or for 6 months after completion of trial treatment
Contra-indication to MRI or gadolinium
Hereditary galactose intolerance, total lactase deficiency or glucose-galactose malabsorption
Known history of current or prior alcohol or drug dependence
Unable to administer oromucosal medication due to mucosal lesions or other issues

CR: complete response; CTCAE: Common Terminology Criteria for Adverse Events; GBM: glioblastoma; IDH: isocitrate dehydrogenase; MGMT: O^6^-methylguanine-DNA-methyltransferase; MRI: magnetic resonance imaging; PR: partial response; SD: stable disease; TMZ: temozolomide

ARISTOCRAT is linked to the Tessa Jowell BRAIN MATRIX (TJBM) programme; utilising the TJBM infrastructure, opening the same participating sites, and aligning the data collection and quality of life assessments already embedded in TJBM [18]. Therefore, patients registered within the TJBM platform who are potentially eligible for ARISTOCRAT may be identified and suggested to sites for consideration in the trial.

### Screening and consent

Written informed consent will be obtained from all patients. The investigator will provide information to allow the patient to make an informed decision regarding their participation. The patient summary and information sheet are provided in Appendix 3, with an exemplar informed consent form in Appendix 4. If a participant loses mental capacity during the study, their responsible caregiver will be consulted to determine their suitability of remaining on trial. Any data collected up to the point of withdrawal will be kept on record and used in the trial analysis. If the patient loses capacity and the caregiver decides that the patient may continue to participate in the trial, then the caregiver will be asked to provide trial related information (e.g., information on side effects) on behalf of the patient.

### Interventions

Patients will be randomised to one of the two treatment arms:

Experimental arm: TMZ with nabiximols.Control arm: TMZ with nabiximols-matched placebo.

All patients will receive non-dose dense TMZ given at 4-weekly intervals (± 3 days for unavoidable delays, bank holidays etc.) up to a maximum of six cycles (pending tolerability) or until disease progression, whichever is sooner. It is recommended that initial doses (in the absence of renal or hepatic impairment) will be:

Cycle 1: TMZ 150mg/m^2^, with dose capping as per local standard practice, once daily (OD) for days 1–5, by mouth (PO), on a 28-day cycle for cycle 1.Cycles 2–6: TMZ 200mg/m^2^, with dose capping as per local standard practice, OD for days 1–5, PO, on a 28-day cycle for cycles 2–6.

Patients who were unable to tolerate 200mg/m^2^ during their initial adjuvant treatment, are permitted to start trial treatment on a lower dose of 150 mg/m^2^ with dose capping as per local standard practice.

Nabiximols or placebo is administered in a self-titration regime (Table 2). This should start as a single spray in the evening of day 1 cycle 1 and gradually titrate to reach an individualised dose based on tolerability. A minimum of three sprays per day is recommended, with the maximum daily dose of 12 sprays. Patients will establish their individualised maximum tolerated dose (MTD) within 14 days of their first dose and continue this regime every day for up to six months (six cycles). If this is not achievable the patient should be permitted to continue in the trial, providing that they continue to receive trial medication, but will not be considered evaluable for the trial and will be replaced.

**Table 2 Tab2:** Nabiximols/placebo titration regimen

Day	Number of Sprays		
	Morning Between waking-up and 12pm	Afternoon Between 4pm and bedtime	Total number of sprays per day
1	0	1	1
2	0	1	1
3	0	2	2
4	0	2	2
5	1	2	3
6	1	3	4
7	1	4	5
8	2	4	6
9	2	5	7
10	3	5	8
11	3	6	9
12	4	6	10
13	4	7	11
14	5	7	12

Taken from the nabiximols Summary of Product Characteristics [29]

This trial uses a non-commercial supply of nabiximols outside its licenced indication, and is a Class B controlled drug under the Misuse of Drugs Act 1971 so is placed in Schedule 2 of the Misuse of Drug Regulations 2001. All trial sites are therefore required to hold an appropriate Home Office licence, or exemption, and to follow Schedule 2 requirements for the storage and dispensing of nabiximols, adding complexity to the pharmacy aspects of this blinded trial.

Patients will be followed up at 4-weekly assessments for a minimum of 52 weeks from the start of trial treatment or until death, whichever is sooner. MRI scanning will be performed at screening, week 10, week 22, week 30, then 3-monthly after commencing trial treatment as per standard practice. A schedule of events is included in Table 3.

**Table 3 Tab3:** ARISTOCRAT trial schedule of events

Activity	Screening Within 21 days of trial entry	Randomisation	Week 0^#^ Cycle 1	Week 4 Cycle 2 ± 3 days	Week 8 Cycle 3 ± 3 days	Week 10 ± 3 days	Week 12 Cycle 4 ± 3 days	Week 16 Cycle 5 ± 3 days	Week 20 Cycle 6 ± 3 days	Week 22 ± 3 days	Week 24 EOT	Follow Up		
												Week 28	Week 30	As per SoC
Informed consent^1^	X													
Confirm eligibility	X													
MRI scan (RANO criteria)^2^	X					X				X			X	X Minimum 3 monthly
Blood tests^3^	X		X	X	X		X	X	X		X			
Concomitant medication^4^	X		X	X	X		X	X	X		X	X		X
Electrocardiogram^5^	X													
Karnofsky Performance Status^6^	X		X	X	X		X	X	X		X	X		X
Medical history^7^	X													
Physical examination^8^	X		X	X	X		X	X	X		X			
Pregnancy test^9^	X		X	X	X		X	X	X		X			
Urine test for cannabinoid use^10^			X		X						X			
Vital signs^11^	X		X	X	X		X	X	X		X			
TMZ + nabiximols/placebo^12^			X	X	X		X	X	X					
Adverse Events^13^	X		X	X	X		X	X	X		X	X		X
Patient diary			X	X	X		X	X	X					
Health-Related Quality of Life^14^			X		X			X			X			
Survival status^14^			X	X	X		X	X	X		X	X		X

# Patients must start trial treatment within 28 days of randomisation

^1^ Written informed consent must be obtained before any trial procedures occur and no greater than 21 days of before randomisation

^2^ Brain MRI scan is ideally performed within 21 days of randomisation. If MRI scan has not been performed within 28 days of start of cycle 1, this will need to be repeated. During trial treatment and follow up, scans must be performed ± 3 days of the scheduled visit

^3^ Blood tests to include: Full blood count (to include Absolute Neutrophil Count and platelets count), urea and electrolytes, liver function tests. During trial treatment, should be performed within 14 days prior to Cycle 1 and within 3 days of Cycles 2–6

^4^ Review of concomitant medication to include dexamethasone and anti-epileptic use

^5^ Single echocardiogram to be performed at Screening only

^6^ Karnofsky Performance Status to be used

^7^ Pseudonymised copy of local pathology report for first diagnosis of GBM must be sent to the ARISTOCRAT Trial Office

^8^ Physical examination to include central and peripheral nervous system examination, required at baseline and subsequently if clinically indicated

^9^ Females of childbearing potential will require a negative pregnancy test (serum or urine) within 7 days prior to randomisationand within 3 days of Cycles 1-6 during treatment.

^10^ Urine sample for cannabinoid use on week 0 (Cycle 1) to be collected pre-dose

^11^ Vital signs to include blood pressure, heart rate, height (screening only) and weight

^12^ Temozolomide (TMZ): 150mg/^2^ for Cycle 1, increasing to 200mg/m^2^ for Cycles 2–6, once daily for days 1–5 at the start of each 28-day cycle

^13^ Adverse Events (AEs) to be documented and reported until the end of treatment visit. During follow up, AEs to be reviewed by Investigator but do not need to be recorded on the AE Form

^14^ HRQoL questionnaires to be completed in clinic at defined visits. HRQoL questionnaires on Week 0 (Cycle 1) to be completed pre-dose

^15^ Follow up visits and assessment will continue until a minimum of 52 weeks from the start of trial treatment or until death, whichever is sooner, as part of standard of care visits. To include documentation of additional hospital or GP visits at follow up visits

Although no additional translational samples will be collected during ARISTOCRAT, patients will provide additional consent for the collection of samples, including archival formalin-fixed paraffin-embedded tumour blocks, to allow for future translational research.

### Treatment compliance

Patients will be asked to complete patient diaries during each cycle of treatment to record the number of TMZ tablets taken and the number of sprays of nabiximols/placebo administered, as well as any side effects experienced. Missed doses will be recorded with reasons. Patients will be asked to return their diaries at their next clinic visit. Urine samples will be collected to check for ‘recreational’ cannabinoid (THC) testing at baseline, cycle three, and at end of treatment. This will be performed by Matrix Diagnostics Ltd. to maintain blinding; positive dipstick tests will receive confirmatory mass spectrometry analysis. Positive tests will not be fed back to sites or patients and will not affect a patient’s continued participation in the trial; however, they may be considered unevaluable at analysis.

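### A positive on-treatment urine THC test may make a patient unevaluable, yet nabiximols contains THC, so exclusion on that result would depend on treatment arm

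*Protocol article*

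**What the plan says.** The Treatment compliance section reads: "Urine samples will be collected to check for ‘recreational’ cannabinoid (THC) testing at baseline, cycle three, and at end of treatment". An outside laboratory does the testing to protect the blind, and "positive dipstick tests will receive confirmatory mass spectrometry analysis". On handling, "Positive tests will not be fed back to sites or patients", and a positive result does not affect continued participation; "however, they may be considered unevaluable at analysis". No criterion is given for when that label applies, to which of the three samples, or to which analysis set.

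Three other places bear on this:

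- The Background describes nabiximols as "an oromucosal spray of a complex botanical mixture containing THC and CBD as the principal cannabinoids".
- The Interventions section has each patient titrate to an individual dose within 14 days and then spray daily for up to six cycles.
- Table 3 puts the urine samples at week 0, week 8 and the week 24 end-of-treatment visit. Only the first has a timing note: "Urine sample for cannabinoid use on week 0 (Cycle 1) to be collected pre-dose".

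The Outcome analyses section defines the primary analysis set by receipt of two or more treatment cycles and does not mention urine results.

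**The concern.** Two of the three samples look for an ingredient of the experimental product while patients are taking it. In the nabiximols arm a positive result at week 8 or week 24 is what good adherence should produce, and it says nothing about outside use. In the placebo arm the same result does point to outside use. The test therefore means different things in the two arms, and the consequence attached to it does not recognise this.

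At stake is a post-randomisation exclusion that depends on arm and is exercised at analysis with no stated criterion. The direction of any bias would depend on how the discretion is used. Applied to everyone with a positive result, it removes nabiximols patients who adhered and reached the sample. Applied only where the result is informative, it removes placebo patients alone.

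**Working it through.** **1. What each sample can show**

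| Sample | Nabiximols arm | Placebo arm |
|---|---|---|
| Week 0, pre-dose | Outside use | Outside use |
| Week 8 (cycle three) | Study drug, outside use or both | Outside use |
| Week 24 (end of treatment) | Study drug, outside use or both | Outside use |

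Only the first row reads the same in both arms. As described, mass spectrometry confirms a positive dipstick; the article does not say that it distinguishes the source of THC.

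**2. The plan's own design figures** (Sample size section: one-sided α 0.10, 80% power, HR 0.68, 2:1, placebo median 12 months, 18 months' accrual, 12 months' follow-up)

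- Hazards: ln 2/12 = 0.0578 on placebo; 0.68 × 0.0578 = 0.0393 on nabiximols.
- Event probability with uniform accrual: P(λ) = 1 − [exp(−12λ) − exp(−30λ)]/(18λ), giving 0.689 and 0.553.
- With 222 patients (74 and 148), events are 51.0 + 81.8 = 132.8, against 132 stated. 222/0.95 = 233.7, rounded up to 234.

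The design figures reproduce, so the sample size is not in dispute.

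**3. How many could be flagged** (the first three inputs are assumptions; none is in the document)

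- 234 at 2:1 gives 156 nabiximols and 78 placebo patients.
- Nabiximols, with 70–90% on drug at week 8 and 80–95% test sensitivity: 156 × 0.70 × 0.80 = 87, to 156 × 0.90 × 0.95 = 133.
- Placebo, with 3–10% outside use: 78 × 0.03 = 2, to 78 × 0.10 = 8.
- For scale, the dropout allowance is 234 − 222 = 12 patients.

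**4. Power if a share f of the nabiximols arm is removed, unrelated to survival**

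Power = Φ(|ln 0.68|/√(1/51.0 + 1/[81.8(1 − f)]) − 1.2816).

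| f | 0 | 10% | 25% | 50% | 75% | 90% |
|---|---|---|---|---|---|---|
| Power | 81% | 80% | 77% | 71% | 58% | 40% |

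**5. Bias if removal applies to nabiximols patients alive at week 8**

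Week 8 is 56/30.4375 = 1.84 months, so exp(−0.0393 × 1.84) = 93% of nabiximols patients are alive then. The values below are large-sample Cox hazard ratios by simulation under the planning hazards, with removal random among week-8 survivors and no placebo patient removed.

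| Share removed | 25% | 50% | 75% | 90% |
|---|---|---|---|---|
| True HR 1, all randomised | 1.05 | 1.13 | 1.39 | 2.08 |
| True HR 0.68, all randomised | 0.71 | 0.76 | 0.93 | 1.38 |
| True HR 1, set requires only starting cycle 2 (week 4) | 1.02 | 1.07 | 1.22 | 1.63 |
| True HR 1, set requires reaching week 8 | 1.0 | 1.0 | 1.0 | 1.0 |

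The primary set is not all randomised patients, so the last two rows are the relevant ones. If two cycles means reaching week 8, a true HR of 0.68 also stays at 0.68. These rows do not cover selection at the end-of-treatment sample, or positivity that tracks adherence and hence prognosis.

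**6. Placebo-only removal**

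Removing 3–10% of placebo patients alive at week 8 or week 24 turns a true HR of 1 into about 0.97–0.995 (same simulation, all randomised patients), slightly in favour of nabiximols.

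**The case against.** The wording is permissive and orders no exclusion. A baseline-only reading is open: a week 0 positive means the same in both arms and fits the eligibility rule on cannabis use within 30 days of randomisation. The assay may measure something that separates the sources. The sentence sits under Treatment compliance, and nothing says that a positive test removes anyone from the survival comparison. Evaluability rules are often left to the full protocol or SAP, which are not shown.

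Much of this stands, and it rules out stronger readings that a reader might infer:

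- That the rule excludes the experimental arm by design, or that most of it will be dropped. The text says only that patients may be considered unevaluable, and the flagged counts rest on assumed inputs.
- That every way of applying the rule depends on arm. Use of the pre-dose sample alone does not.
- That confirmation can only detect study drug. The analytes are not stated.
- That the survival bias has the size seen in all randomised patients. The two-cycle requirement removes much or all of the week-8 part.

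What the objection does not answer is that the article attaches the consequence to positive tests in general, having named three timepoints, two of them during or at the end of daily THC dosing. This is a stated consequence that those two samples cannot support in the nabiximols arm, not just missing detail. Discretion over a result that can reveal allocation adds to the risk. A restriction in the SAP would still leave this sentence needing correction.

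**Conclusion.** The point holds in a limited form. As written, the article permits exclusion on on-treatment THC results that cannot identify outside use in the nabiximols arm by any described step, and acting on them would make the exclusion depend on arm.

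The size is conditional. Exclusion across both arms would cost power: from about 81% to 71% if half the nabiximols arm were removed, and to 58% if three quarters were. It could also bias the comparison against nabiximols, though little or not at all from week-8 survival selection if the two-cycle set means reaching week 8. Placebo-only exclusion would give a small bias towards nabiximols. How many patients would be affected cannot be derived from the document; 87–133 of 156 is an upper scenario, not a forecast. The conclusion assumes that the assay does not separate sources of THC, since no such step is described, and that the unevaluable label could reach the primary overall survival comparison, which the article neither states nor rules out.

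**What to change.** In the Treatment compliance section, state that:

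- no on-treatment urine result removes a patient from the primary overall survival analysis set;
- placebo-arm on-treatment results are used only to describe contamination, and nabiximols-arm results only as an exposure check;
- any THC-based exclusion is confined to a sensitivity analysis that uses the pre-dose week 0 sample and applies identically in both arms.

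This should be settled before unblinding and carried into the SAP. It takes a few sentences and leaves sampling, laboratory work and blinding unchanged. It does not require changing the two-cycle primary population, which is a separate question. The small downside is that outside cannabis users stay in the primary analysis, which may slightly dilute the estimated effect.
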